**4. Participant Recruitment**

**Inclusion Criteria**:

- Adults aged ≥18 years.
- Partial edentulism (missing one or more teeth in an arch with remaining natural teeth).
- Sufficient bone volume and quality for implant placement (confirmed by CBCT).
- No systemic contraindications for surgery.

**Exclusion Criteria**:

- Uncontrolled systemic diseases (e.g., uncontrolled diabetes).
- Smokers or patients with a history of non-compliance with postoperative care.
- Patients requiring bone grafting or sinus lifts.

**Recruitment Process**: Patients will be recruited from dental clinics at King Khalid University. Eligible patients will receive detailed study information and provide written informed consent. Recruitment will occur between January 6 and February 3, 2025.

**5. Ethical Considerations**

This study adheres to the Declaration of Helsinki and Good Clinical Practice guidelines. Key ethical considerations include:

**Informed Consent**:

- All participants will provide written informed consent after receiving comprehensive information about the study’s purpose, procedures, risks, benefits, and their right to withdraw at any time without penalty.
- Consent forms will be available in Arabic and English, ensuring accessibility.

**Risks and Benefits**:

- **Risks**: Potential risks include surgical complications (e.g., infection, nerve injury), pain, swelling, and implant failure, which are inherent to dental implant procedures. These will be minimized through standardized protocols, experienced surgeons, and rigorous postoperative monitoring.
- **Benefits**: Participants will receive high-quality implant treatment at no cost, potentially improving oral function and aesthetics. The study will contribute to evidence-based implant dentistry, benefiting future patients.

**Confidentiality**:

- Patient data will be anonymized using unique identifiers. Data will be stored in a secure, password-protected database accessible only to authorized personnel.
- Only de-identified data will be used for analysis and publication.

**Adverse Event Management**:

- Adverse events (e.g., complications, implant failure) will be monitored and reported to the ethics committee within 24 hours.
- Participants experiencing adverse events will receive immediate clinical care per standard protocols.

**Voluntary Participation**:

- Participation is voluntary, and patients can withdraw at any time without affecting their access to standard care.

**6. Methodology**

**Randomization**: Computer-generated randomization (1:1:1 ratio), stratified by age and gender, will assign participants to FHIS, PDIS, or FGIS groups.

**Blinding**: Surgeons and participants cannot be blinded due to the nature of the interventions. Outcome assessors (radiologists, statisticians) will be blinded to group allocation to reduce bias.

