**2. Study Objectives**

**Primary Objective**: To compare the efficacy of freehand, pilot-drilled, and fully guided implant surgery in partially edentulous patients with respect to surgical outcomes (duration, complications), postoperative recovery (pain, swelling), implant stability, osseointegration, and patient satisfaction.

**Secondary Objectives**: To evaluate long-term implant success rates and summarize the advantages and limitations of each technique to optimize clinical protocols.

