**Key Outcomes**:

- Surgical duration (minutes).
- Implant placement accuracy (via postoperative CBCT).
- Postoperative complications (within 30 days).
- Early implant failure rates (within 6 months).
- Patient satisfaction (via validated 10-point questionnaire at 6 months).
- Implant stability (via Resonance Frequency Analysis at 3, 6, and 12 months).
- Pain and swelling (via Visual Analogue Scale on Days 1 and 3).

**Study Duration**: January 6, 2025 (recruitment start) to August 3, 2025 (final follow-up).
**Sample Size**: 90 patients (30 per group), calculated for 80% power and alpha of 0.05, assuming a medium effect size (Cohen’s d = 0.5) for implant placement accuracy, with a 10% dropout rate.

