**Statistical Analysis**:

- Descriptive statistics: Mean, SD for continuous variables; frequencies for categorical variables.
- Normality testing: Shapiro-Wilk test.
- Comparative analysis: One-way ANOVA with Tukey post hoc test for group differences.
- Subgroup analysis: Canine vs. molar implants.
- Software: SPSS (Version 23).
- Significance level: $p < 0.05$.
- Analysis will follow an intention-to-treat approach.

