**4. Imaging Parameters**

To ensure reproducibility and diagnostic accuracy, the following standardized parameters will be used:

- **Field of View (FOV)**:
  - Small FOV (5x5 cm or 8x8 cm) for single-tooth or small-segment edentulous areas.
  - Medium FOV (10x10 cm) for larger edentulous spans or multiple implants, ensuring inclusion of adjacent teeth and anatomical landmarks (e.g., inferior alveolar nerve, maxillary sinus).
- **Voxel Size**: 0.2 mm for high-resolution imaging to assess fine bone details and implant positioning.
- **kVp**: 90 kVp (range: 80–100 kVp, adjusted based on patient size to optimize image quality).
- **mA**: 5–10 mA, adjusted to minimize radiation dose while ensuring diagnostic clarity.
- **Exposure Time**: 10–15 seconds, depending on the FOV and patient cooperation.
- **Rotation**: 360° for comprehensive 3D reconstruction.
- **Image Format**: DICOM (Digital Imaging and Communications in Medicine) for compatibility with implant planning software.

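### Number of implants per patient is left open but is neither adjusted for nor stratified on, and the unit of surgical duration is undefined: a loss of precision, not a bias, that a covariate would largely recover

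*Protocol*

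**What the plan says.** - **Eligibility (section 4).** Entry requires "Partial edentulism (missing one or more teeth in an arch with remaining natural teeth". No maximum number of teeth or implants is set. The exclusion "Patients requiring bone grafting or sinus lifts" limits complexity but not extent.
- **CBCT imaging protocol, section 4.** It provides for single-tooth areas and also for larger cases: "Medium FOV (10x10 cm) for larger edentulous spans or multiple implants".
- **Randomisation (section 6).** "Computer-generated randomization (1:1:1 ratio), stratified by age and gender".
- **Objectives (section 2).** The primary objective covers "surgical outcomes (duration, complications), postoperative recovery (pain, swelling), implant stability, osseointegration, and patient satisfaction".
- **Key Outcomes (section 3).** The duration outcome reads "Surgical duration (minutes", with no statement of per patient, per session or per implant. The data collection list in section 6 adds nothing on this.
- **Statistical Analysis (section 6).** "One-way ANOVA with Tukey post hoc test for group differences". The only site-related analysis is "Subgroup analysis: Canine vs. molar implants", which concerns position and not number.

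**The concern.** An operation that places three implants can be expected to take longer than one that places a single implant, whatever the technique. If duration is timed per operation, the number of implants is a strong predictor of it. That number can be known beforehand, because the preoperative assessment plans the implant positions. The protocol neither balances it between arms nor adjusts for it.

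Two things are at stake. The spread between small and large cases goes into the error term of the ANOVA and lowers power. And with 30 patients per arm, the arms may differ by chance in case extent, so that one realised comparison of duration is hard to interpret. Pain and swelling on Days 1 and 3 may be affected in the same way. That link is reasoned and is not quantified here. The issue concerns outcomes with one value per patient, so it is separate from clustering of implants within patients.

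**Working it through.** **Plan's own figure.** There is none for duration. The sample-size statement concerns placement accuracy and does not bear on this point.

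**Inputs from the protocol.** 3 arms of 30 (N = 90), alpha 0.05, one-way ANOVA, stratification by age and gender only.

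**Assumptions (not in the documents).** Duration timed per operation; b = 15 min per extra implant; residual SD s = 10 min; a true difference of 8 min in one arm; four mixes of 1/2/3/4 implants per patient.

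**Step 1, power.** With one arm of three shifted by 8 min, the between-arm variance is 8² × 2/9 = 14.22, and N × 14.22 = 1280.

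- Unadjusted: noncentrality λ = 1280 / (b² × Var(n) + s²) = 1280 / (225 × Var(n) + 100), F on 2 and 87 df.
- Adjusted for number of implants: λ = 1280 / 100 = 12.8, F on 2 and 86 df, giving power of about 89%.

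| Mix of 1/2/3/4 implants (%) | Var(n) | 225 × Var(n) + 100 | λ | Power, unadjusted |
|---|---|---|---|---|
| 90/10 | 0.09 | 120.25 | 10.64 | 83% |
| 70/20/10 | 0.44 | 199.00 | 6.43 | 60% |
| 50/25/15/10 | 1.0275 | 331.19 | 3.86 | 39% |
| 40/25/20/15 | 1.19 | 367.75 | 3.48 | 36% |

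Simulation of the same settings agrees to within about a percentage point (unadjusted 83%, 60%, 39% and 35%; adjusted 88–89%).

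**Step 2, type I error.** With no technique effect, simulated rejection by the unadjusted ANOVA is 5.0–5.2% under every mix. The overall error rate is kept.

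**Step 3, chance imbalance.** If 30% or 50% of patients have more than one implant, the largest and smallest arm shares differ by at least 20 percentage points in about 27% or 33% of trials. At 10% multi-implant patients the figure is about 5%.

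A gap of that size is modest in minutes. With 1–3 implants per patient (50/30/20 or 70/20/10), 10–20 min per extra implant and residual SD 10–15 min, multi-implant patients have on average 1.33–1.4 extra implants. The shift is therefore 0.20 × 1.33 × 10 = 2.7 min to 0.20 × 1.4 × 20 = 5.6 min, or 0.6–1.2 standard errors of a two-arm difference. Tukey significance needs about 2.4.

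Larger gaps can mislead. With the Step 1 values and no technique effect, arm means differ by at least 0.5 implants in none, about 1%, 15% and 19–20% of trials across the four mixes. Within those trials the unadjusted ANOVA rejects in 46–48%, 25–27% and 22% for the last three mixes.

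**Step 4, variance share.** Under the wider assumptions of Step 3, number of implants explains b² × Var(n) / (b² × Var(n) + s²) of the variance in duration. The lowest value is 100 × 0.44 / (44 + 225) = 16%, and the highest is 400 × 0.61 / (244 + 100) = 71%.

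**The case against.** Two stronger readings are tempting, and the documents support neither.

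- **That the trial compares total operating minutes.** A reader might infer this, but the protocol says only minutes. If time is recorded per implant, the argument on duration largely falls away. What can be said is that the unit is undefined while case size varies.
- **That case extent rather than technique will drive the result.** This suggests confounding. Randomisation balances case extent in expectation, and the ANOVA error term already allows for chance imbalance, as Step 2 shows. A single realised trial can still be distorted, but no direction is built in.

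Three further objections deserve weight. The magnitudes rest wholly on assumed values, and with mostly single-implant patients there is little to gain. That stands, although the protocol neither gives the mix nor restricts entry to single-implant cases. Choosing stratification factors is a judgement, and exchanging gender for number of implants is a trade-off rather than a correction. That stands too, so no such exchange is asked for. Finally, covariates are often left to a statistical analysis plan, which is not at hand. That carries less weight here, because the protocol is not silent: it names a one-way ANOVA. A later plan could add the covariate, but only by departing from that stated method.

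**Conclusion.** The point holds as a matter of precision. The protocol leaves the number of implants open, uses it in neither the randomisation nor the analysis, and does not define the unit of duration. If duration is per operation, the comparison remains valid and its type I error stays near 5%. Under the Step 1 assumptions, however, power for an 8-minute difference is 36–83% instead of about 89%, and when many patients have several implants a chance imbalance can make one result hard to read. With about 90% single-implant patients the loss is only about 6 percentage points (89% against 83%). None of this invalidates the design. It is a nearly free improvement to an outcome named in the primary objective. The extension to pain and swelling rests on reasoning alone.

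**What to change.** - **Key Outcomes (section 3).** State that surgical duration is minutes per operation, and record the number of implants for each patient.
- **Statistical Analysis (section 6).** For surgical duration, and likewise for pain and swelling, replace the unadjusted ANOVA with a linear model (ANCOVA) of arm plus preoperatively planned number of implants, with Tukey-adjusted comparisons of the adjusted means. Use the planned number, fixed before allocation, and not the number placed, so that the covariate cannot be affected by the technique.
- **Randomisation (section 6), optional.** If the list is not yet fixed, stratification by one versus two or more planned implants could be considered. Gender need not be dropped, and the covariate alone recovers most of the lost power.

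The cost is one sentence in the outcome definition, one field on the case report form if it is not already there, one analysis line and one degree of freedom. No extra patients, visits or scans are needed.

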**Preoperative Assessment**:

- Comprehensive dental and medical history.
- Clinical examination and CBCT for bone assessment.
- Impressions for study models to plan implant positions.

**Interventions**:

- **FHIS**: Implants placed using clinical judgment, with minimal surgical guides.
- **PDIS**: Pilot drill used for initial osteotomy, followed by sequential drilling.
- **FGIS**: Customized surgical guides based on CBCT and planning software ensure precise implant placement.

**Data Collection**:

- Baseline: Demographics, medical history, CBCT findings.
- Intraoperative: Surgical duration, complications.
- Postoperative: Pain, swelling, complications, RFA scores, and patient satisfaction at specified intervals.
- Data will be recorded in standardized case report forms and stored securely.

**Statistical Analysis**:

- Descriptive statistics: Mean, SD for continuous variables; frequencies for categorical variables.
- Normality testing: Shapiro-Wilk test.
- Comparative analysis: One-way ANOVA with Tukey post hoc test for group differences.
- Subgroup analysis: Canine vs. molar implants.
- Software: SPSS (Version 23).
- Significance level: $p < 0.05$.
- Analysis will follow an intention-to-treat approach.

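### Pain, swelling and implant stability are repeated measures, but the only comparative test is a one-way ANOVA with no visit term and no rule across visits

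*Protocol*

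**What the plan says.** Section 2 (Study Objectives) puts "postoperative recovery (pain, swelling), implant stability, osseointegration, and patient satisfaction" inside the primary objective. Three of these outcomes are then scheduled more than once per patient under Key Outcomes in section 3: "Pain and swelling (via Visual Analogue Scale on Days 1 and 3" and "Implant stability (via Resonance Frequency Analysis at 3, 6, and 12 months". The Data Collection paragraph of section 6 confirms this: "Postoperative: Pain, swelling, complications, RFA scores, and patient satisfaction at specified intervals".

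The Statistical Analysis paragraph of section 6 gives one comparative method for all outcomes: "Comparative analysis: One-way ANOVA with Tukey post hoc test for group differences". Its only factor is group. The protocol names no patient or visit term, no single visit as the one that counts, and no rule for combining or ranking the visits. The significance level is 0.05 throughout.

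**The concern.** A one-way ANOVA by group fits an outcome measured once. For an outcome measured two or three times on the same person, it leaves open how the visits enter the analysis.

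With one ANOVA per visit, each outcome yields two or three separate answers, and nothing says which of them decides. An arm could be called better on whichever visit falls below 0.05. A single-visit test also ignores what the other visit says about the same patient, and no combination of separate tests estimates a difference between arms in change over time. With 30 patients per arm there is little power to spare.

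This does not depend on patients having several implants. It arises with one implant each.

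**Working it through.** **Inputs.** From the protocol: 30 per arm (section 3), or 30 × 0.9 = 27 after the 10% dropout; alpha 0.05; two visits for pain and swelling. Assumed, because the protocol gives no value: within-patient correlation ρ = 0.5 (range 0.3 to 0.7), and equal variance at each visit. The effect size is borrowed for illustration: the protocol states d = 0.5 only for placement accuracy ("assuming a medium effect size (Cohen’s d = 0.5) for implant placement accuracy"). Arm means are set at 0, 0.25 and 0.5 SD. Three-visit results are not used, because the 12-month stability reading does not fit the study dates of 6 January to 3 August 2025.

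**1. The plan's own figure.** The protocol gives no power for the repeated outcomes. Its one figure is 30 per arm, "calculated for 80% power and alpha of 0.05", and this is not reproduced. A two-sided comparison of two arms needs n = 2 × (1.960 + 0.842)² / 0.5² = 62.8, so 63 per arm, and 63/0.9 = 70 with dropout. That is a separate matter and nothing below rests on it, but it explains why the powers below are far from 80%.

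**2. One ANOVA per visit: error rate.** Each test holds 5% (4.9% to 5.2% across the simulated settings). For two independent visits, the chance that at least one is falsely significant is 1 − 0.95² = 9.75%. With correlated visits (simulation, 40,000 trials per setting, 30 per arm) it is 9.7%, 9.2% and 8.7% for ρ = 0.3, 0.5 and 0.7; at 27 per arm it is 9.6%, 9.1% and 8.5%. Tukey does not touch this, because it adjusts over pairs of arms within one ANOVA.

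**3. Power when the effect is the same at both visits.** The omnibus F-test has non-centrality λ = n Σ(μⱼ − μ̄)² / σ², with 2 and 87 degrees of freedom.
- Single visit: λ = 30 × (0.25² + 0 + 0.25²) / 1 = 3.75, power 38%.
- Mean of two visits, which for balanced data gives the group effect of a repeated-measures model: σ² = (1 + ρ)/2 = 0.65, 0.75, 0.85, so λ = 5.77, 5.00, 4.41 and power is 55%, 49%, 44%.
- At 27 per arm: 34.5% for one visit against 50%, 45%, 40%.

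**4. Power when the effect fades.** The averaged contrast then works on a smaller difference.
- Second-visit effect half the first: averaged d = (0.5 + 0.25)/2 = 0.375. At ρ = 0.5, λ = 30 × 2 × 0.1875² / 0.75 = 2.81, power 29% (33% to 26% for ρ = 0.3 to 0.7).
- Effect at one visit only: averaged d = 0.25. At ρ = 0.5, λ = 30 × 2 × 0.125² / 0.75 = 1.25, power 15% (17% to 14%).
- The ANOVA at the affected visit keeps 38% in both cases.

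**5. Visits stacked as independent rows, which the protocol does not state.** An arm mean over two visits has variance (1 + ρ)/(2n). The stacked ANOVA takes it as about (1 + s²/4)/(2n), where s is the mean change between visits in SD. The two agree at s = 2√ρ, that is 1.10, 1.41 and 1.67 SD for ρ = 0.3, 0.5 and 0.7. Below that the test rejects too often, above it too seldom. Simulated type I error at 30 per arm:
- No change between visits: 10.1%, 14.0%, 17.6% for the three correlations.
- ρ = 0.5 with a change of 1, 1.5 and 2 SD: about 8%, 4% and 2%.

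**The case against.** The strongest reply is that nothing here is invalid. The protocol lists distinct time points, so the natural reading is one ANOVA per time point, and each is a sound 5% test with a clear meaning. The objectives do not ask about change over time, so the lack of a group-by-visit test contradicts nothing. How visits enter a model is often left to a statistical analysis plan, which is not at hand here. The either-visit problem is also part of a wider lack of one primary endpoint.

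Much of this stands. The per-visit tests are valid, and the missing interaction test is a limitation, not a contradiction. But the protocol is not silent on method. It fixes one named test for all outcomes, including three in the primary objective that it does not fit, and a later plan with a repeated-measures model would depart from this text.

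A second reply is that a mixed model can do worse. That is also right: an averaged contrast falls to 29% or 15% if the effect fades or exists at one visit only. It limits which contrast should lead, but not the case for modelling the visits together. Conversely, declaring success at either visit reaches 54% power when the effect is equal (ρ = 0.5), above the 49% of the average, but only by spending about 9% error.

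A reader might infer that the visits will be pooled as independent rows and that the false-positive rate is therefore inflated. The documents do not support this. Nowhere do they say that visits are stacked, and if they were, the error could fall on either side of 5%, depending on a mean change between visits that the protocol does not give.

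**Conclusion.** The point holds as a mismatch between design and stated analysis, of moderate weight. On the ordinary reading, what is wrong is not the level of any one test. It is the absence of a rule across visits (about 9% chance of a false positive at one or other of two visits), the inability to compare change over time, and the power forgone when the effect is similar at both visits: 6 to 17 points at 30 per arm (38% against 44% to 55%).

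The error figure rests on the assumed correlation. The power figures rest as well on an effect size that the protocol gives for another outcome and on equal effects at the two visits. If effects are unequal, the gain shrinks and can reverse. The conflict between the 12-month stability visit and the study dates is a separate issue that this conclusion does not need.

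**What to change.** In the Statistical Analysis paragraph of section 6, keep one-way ANOVA with Tukey for outcomes measured once. For pain, swelling and resonance frequency stability, specify one linear mixed model per outcome, with group, visit and group-by-visit as fixed effects and within-patient correlation across visits (a random patient effect or an unstructured covariance).

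Name one main comparison per outcome in advance. Use the visit-averaged group contrast if a similar effect is expected across visits; otherwise use a single pre-named visit from the same model. Make pairwise arm contrasts Tukey-adjusted, and report the remaining per-visit contrasts and the group-by-visit term as supportive.

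The cost is analysis wording only: no new data, visits or patients, and the MIXED procedure in the named software fits the model. The price of leading with the average should be stated alongside it: about 29% power if the effect halves by the second visit and 15% if it is present at one visit only, against 38% for a test at the affected visit (ρ = 0.5, 30 per arm).

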**2. Scope**

This protocol applies to all 90 participants enrolled in the RCT, covering preoperative and postoperative CBCT scans for the freehand (FHIS), pilot-drilled (PDIS), and fully guided (FGIS) implant surgery groups.

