**5. Preoperative CBCT Procedure**

**Purpose**: To assess bone volume, density, and anatomical structures for implant planning. **Timing**: Performed within 2 weeks before surgery.

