**8. Data Management**

- **Storage**: DICOM files will be stored in a secure, password-protected database with unique patient identifiers to ensure confidentiality.
- **Access**: Only authorized study personnel (radiologists, investigators) will access imaging data.
- **Analysis**: Images will be analyzed using validated software to quantify implant placement accuracy and bone characteristics.
- **Retention**: Imaging data will be retained for 5 years post-study, per institutional guidelines, and then securely deleted.

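### Preoperative CBCT bone density, a candidate covariate collected in every participant, goes unused because the protocol fixes an unadjusted one-way ANOVA for implant stability; the possible cost is precision, not validity

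*Protocol*

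**What the plan says.** Protocol section 2 puts implant stability in the primary objective, and section 3 (Key Outcomes) schedules it as "Implant stability (via Resonance Frequency Analysis at 3, 6, and 12 months". No preoperative or at-placement RFA is listed there.

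Section 6 (Statistical Analysis) gives one comparative method for all outcomes: "Comparative analysis: One-way ANOVA with Tukey post hoc test for group differences". It names no covariate. Randomisation is stratified by age and gender only.

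Bone is measured before surgery in everyone:
- CBCT imaging protocol, section 2: "This protocol applies to all 90 participants enrolled in the RCT".
- CBCT imaging protocol, section 5, on the purpose of the preoperative scan: "To assess bone volume, density, and anatomical structures for implant planning".
- Section 6 (Data Collection): "Baseline: Demographics, medical history, CBCT findings".
- CBCT imaging protocol, section 8: "Images will be analyzed using validated software to quantify implant placement accuracy and bone characteristics".

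The protocol uses the preoperative bone data for eligibility ("Sufficient bone volume and quality for implant placement (confirmed by CBCT") and for planning the implant. It does not use them in any stated comparison of the arms.

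**The concern.** A baseline variable correlated with the outcome removes variance from the error term when it enters the model, and the comparison between techniques gets narrower intervals from the same patients. Bone density at the implant site is a natural candidate for RFA. It is specific to the site, it is measured before the technique can affect it, and there is no baseline RFA to adjust for instead. The entry criterion sets a minimum and does not make bone uniform among those enrolled.

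This is more than an unfinished detail that a statistical analysis plan would fill in. The protocol names a specific model, and that model has no place for a covariate, so a later plan would have to replace it. At stake is the precision of the stability comparison, in a trial with only 30 patients per arm.

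**Working it through.** **Inputs from the protocol.** Three arms and "90 patients (30 per group), calculated for 80% power and alpha of 0.05"; Cohen's d = 0.5, stated for placement accuracy; 10% dropout, so 30 × 0.9 = 27 evaluable per arm.

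**Inputs not in the protocol.** The within-arm correlation rho between bone density and RFA; an effect size or SD for RFA; whether tests are two-sided. I take rho from 0 to 0.6, borrow d = 0.5 purely as an illustration, and test two-sided.

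**The plan's own figure first.** For a two-sided comparison of two means, n per arm = 2 × (1.960 + 0.842)² / 0.5² = 2 × 7.849 / 0.25 = 62.8, so 63. Allowing for dropout, 63 / 0.9 = 70 per arm, or 210 in total. The stated 90 is not reproduced. An overall F-test at f = 0.25 does not reproduce it either: it needs 53 per arm, 159 in total, before dropout. The trial therefore starts well below 80% power at d = 0.5.

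**Effect of one covariate.** The residual variance is multiplied by (1 − rho²), so the standard error is multiplied by √(1 − rho²), and n patients per arm act like n / (1 − rho²). This ignores the small extra term from chance imbalance in the covariate.

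**Pairwise power, 27 per arm.** Effective d = 0.5 / √(1 − rho²). Noncentrality = effective d × √(27/2). The error is pooled over three arms, with 81 − 3 = 78 degrees of freedom unadjusted and 77 with one covariate. The critical t is 1.99 without multiplicity control and 2.39 with Tukey. Unadjusted, the noncentrality is 0.5 × 3.674 = 1.837. At rho = 0.5 it is 0.577 × 3.674 = 2.121.

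| rho | fall in SE | 27 per arm acts like | power, no multiplicity control | power, Tukey |
|---|---|---|---|---|
| unadjusted | – | 27.0 | 44.2% | 29.6% |
| 0.1 | 0.5% | 27.3 | 44.6% | 29.9% |
| 0.2 | 2.0% | 28.1 | 45.7% | 30.9% |
| 0.3 | 4.6% | 29.7 | 47.7% | 32.7% |
| 0.4 | 8.3% | 32.1 | 50.8% | 35.5% |
| 0.5 | 13.4% | 36.0 | 55.4% | 39.9% |
| 0.6 | 20.0% | 42.2 | 62.1% | 46.6% |

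With all 30 per arm, Tukey power is 33.2% unadjusted and 44.4% at rho = 0.5.

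**Cost if the covariate is useless.** At rho = 0 the lost degree of freedom costs less than 0.1 percentage point of power.

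**Limit of the remedy.** In a plain two-arm normal calculation without multiplicity control, rho would have to reach about 0.72 with 30 per arm, or 0.75 with 27, for 80% pairwise power at d = 0.5.

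**The case against.** The strongest objection is that the relationship itself is assumed. Nowhere does the protocol say that CBCT bone density or volume predicts RFA, and it gives no correlation. A reader might infer from the collected data that bone density is an established predictor and that precision is certainly being lost. The documents support only that it is a candidate and that precision may be lost. Several features could make rho low: the requirement for sufficient bone and the exclusion of patients needing grafts or sinus lifts narrow its range, and CBCT imaging protocol section 4 lets kVp, mA and field of view vary, which may add noise to a density reading. At rho = 0.3 the illustrative gain is only about 3 points. This objection stands, and it is why the size is given as a range.

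A reader might also infer bias: with 30 per arm, bone density could differ between arms by chance and move the RFA means. That does not make the unadjusted ANOVA wrong. Under randomisation its tests and intervals already allow for chance imbalance in unmodelled variables. Adjustment would sharpen the estimate; it would not rescue an invalid one.

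It can further be said that covariates belong in the statistical analysis plan. That would carry weight if the protocol had left the model open, but it names one.

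Lastly, the covariate is not ready to use. No density scale, region of interest or volume metric is defined, and the postoperative scan also assesses bone. This stands and shapes the fix.

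**Conclusion.** The point holds as a conditional matter of efficiency. Bone is assessed before surgery in every participant and is to be quantified, and the model fixed for RFA cannot use it. The planned test remains valid.

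The reduction in standard error is about 0.5% at rho = 0.1, 5% at 0.3 and 13% at 0.5. In the illustration, Tukey pairwise power moves from 30% to 30%, 33% and 40%. These power figures rest on an assumed rho, on a d borrowed from another outcome, on two-sided tests and on 27 evaluable per arm. The percentage falls in standard error depend on rho alone, apart from small-sample terms.

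The balance favours adjustment: almost nothing is lost if rho is near 0, and a useful amount is gained if it is moderate. It does not make up the shortfall against the stated 80% power, which is a separate and larger problem.

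**What to change.** In protocol section 6 (Statistical Analysis), replace the one-way ANOVA for RFA by an ANCOVA:

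- **Factor:** randomised arm.
- **Covariate:** one prespecified, continuous bone-density measure at the implant site, taken from the preoperative scan only so that the technique cannot affect it. State the scale, the region of interest and the software.
- **Unit:** one density value and one RFA value per patient, each the mean over sites where there are several implants.
- **Comparison:** adjusted arm means, with Tukey as now.
- **Sensitivity analysis:** the unadjusted one-way ANOVA.

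State the RFA visits to which the model applies. The 12-month reading falls after the final follow-up of August 3, 2025 given in section 3, so those two statements need reconciling first.

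The cost is a short paragraph, one residual degree of freedom, and the work of extracting the density measure in the same way from scans already planned. No new patient, visit or scan is needed. The downside is that the gain may be small if rho is low.
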